## Abstract

**Background:**

Smoking and resulting health problems disproportionately impact low socioeconomic status (SES) individuals. Building resilience presents an approach to ‘closing the gap’. Mindfulness-based interventions and setting realistic goals are preferred in low socioeconomic communities. We aim to test if these interventions, delivered online and consolidated with peer support offered via ex-smokers, are successful in promoting smoking cessation and resilience. Our conceptualisation of resilience encompasses the inner capacity/skills and external resources (e.g., social support) which smokers utilise to bounce back from adversity. We include a process evaluation of barriers/facilitators to interventions and cost-effectiveness analysis (from health system perspective).

**Methods:**

We plan a four-arm parallel 12-month RCT with a 6-month follow-up to test the efficacy of three group-based interventions each followed by peer support. Arm 1: mindfulness-integrated cognitive behavioural therapy; Arm 2: mindfulness training; Arm 3: setting realistic goals; Arm 4: active control group directed to quit services. All interventions will be administered online. Participants are adult smokers in Australia (N = 812) who have an average weekly household income less than $457AUD or receive welfare benefits. Group-based interventions will occur over 6 months, followed by 6 months of forum-based peer support. Primary outcome: self-reported 14-day period prevalence of smoking abstinence at 6 months, with remote biochemical verification of saliva cotinine (< 30 ng/mL). Secondary outcomes include: internal resilience (Connor-Davidson Resilience Scale-25); external resilience (ENRICHD social support tool); quality adjusted life years (EQ-5D-5L); self-efficacy for smoking abstinence (Smoking-Abstinence Self-Efficacy Questionnaire); motivation to quit smoking (Biener and Abrams Contemplation Ladder); nicotine dependence (Fagerstrom Test for Nicotine Dependency); equanimity (Equanimity Scale-16); stress (Perceived Stress Scale-10); goal assessment/attainment (Problems and Goals Assessment Scale).

**Discussion:**

This study is the first to compare resilience interventions for low SES smokers which have been identified by them as acceptable. Our various repeated measures and process evaluation will facilitate exploration of mechanisms of impact. We intervene within the novel framework of the Psychosocial Model of Resilience, applying a promising paradigm to address a critical and inequitable public health problem.

*Trial registration* Australian New Zealand Clinical Trials Registry ID: ACTRN12621000445875, registered 19 April 2021 (https://anzctr.org.au/Trial/Registration/TrialReview.aspx?id=381007&isReview=true). The Universal Trial Number is U1111-1261–8951

**Supplementary Information:**

The online version contains supplementary material available at 10.1186/s13722-022-00355-w.

## Background

Smoking tobacco is a leading cause of preventable death globally, resulting in approximately eight million deaths each year when including the impact of second-hand smoke. [1] Diseases associated with smoking—such as lung cancer, heart disease, and stroke—are, if not fatal, detrimental to quality of life. In Australia, for instance, an estimated six million quality adjusted life years (QALYs) will be lost from smoking if the current population of smokers is tracked until 70 years of age. [2] Globally, the economic burden on healthcare systems and lost productivity from smoking-attributable diseases in 2012 was estimated at purchasing power parity of $1852 billion for the year, or 1.8% of the world’s annual gross domestic product. [3]

Although population prevalence of smoking is generally decreasing in high-income countries, [1] those in socioeconomically disadvantaged groups are less successful at quitting and are over-represented in smoking statistics. [4] Socioeconomic status (SES) is a broad concept which refers to the position of an individual, family, or group within the socioeconomic hierarchy, and as it relates to health, the consequential environment and access to basic resources. [5] It is typically measured by one or several of the following factors: income/wealth, education, and occupation—though in practice, the categorisation of SES will vary between countries and over time. Individuals from lower SES environments are more likely to try smoking, smoke regularly, [4] and die prematurely from smoking-attributable diseases. [6] Furthermore, smokers in this group are likely to have a higher nicotine dependence. [7, 8] Although low SES individuals are likely to make quit attempts at a similar rate to other socio-economic strata, they are less likely to succeed. Kotz and West [9] found that the success rate of quit attempts among those in the highest socioeconomic level was 20.4%, compared to 11.4% for those in the lowest socioeconomic level, but found no socioeconomic-related differences in the rate of quit attempts.

Building resilience could be vital for promoting smoking cessation in low SES groups. This asset-based approach focuses on building strengths, capabilities, and protective factors, as opposed to fixating on deficits of people or groups. [10–15] Resilience is defined not merely as coping with perceived difficulties but “bouncing back from adversity” and finding hope and meaning. [16] Our conceptual model of resilience (Fig. 1; [15, 17]) extends this notion beyond the internal properties of the individual (internal resilience) and into the social environment and interpersonal resources (external resilience). Internal factors such as self-efficacy, self-confidence, and motivation are often important for building resilience and hence making successful quit attempts. However, individuals with a lower SES, on average, have significantly lower levels of motivation and self-efficacy compared to higher SES individuals. [4, 8, 18–22] These factors are correlated with feelings of powerlessness, less social support, higher perceived stress eroding motivation, and normalisation of smoking behaviour. [8, 23] Given these multifarious obstacles to cessation faced by low SES individuals and the proposed interplay between internal and external resources (Fig. 1), building resilience presents as a promising approach from which to empower low SES individuals to change their smoking behaviour.

**Fig. 1 Fig1:**
[figure not shown]
The psychosocial interactive model of resilience [17]

The Behaviour Change Wheel [24] is the guiding framework for resilience interventions for smoking cessation in the present study. It synergises with the Psychosocial Model of Resilience because it describes a comprehensive system of behaviour change interventions that acknowledges the capabilities, opportunities, and motivation necessary for smoking cessation. Tsourtos et al. [25] used the Nominal Group Technique to approach a consensus regarding the feasibility and acceptability of six evidence-based resilience interventions among diverse representatives from low SES backgrounds. Setting realistic goals and mindfulness-based interventions were considered the most feasible and appropriate and have therefore been selected for the present study.

Setting goals is one of the most common behaviour change techniques for smoking cessation. [25–27] Goals help regulate behaviour by motivating an individual to reduce the difference between current and desired circumstance. [28] Achieving small goals on the way to tackling more difficult goals can build self-efficacy, confidence, and feelings of agency. [29, 30] Conversely, research suggests that higher quality goals (i.e., clear, proximal quit dates of complete abstinence) can increase the probability of a successful quit attempt. [31] Although specific research on goal setting as a standalone intervention for smoking cessation is scarce, the ability to aid smokers in constructing goals is a critical evidence-based competency for practitioners providing behavioural support. [32] Furthermore, a meta-analysis of 37 intervention studies concluded that goal setting was one of nine techniques which demonstrated the most promising efficacy and feasibility. [27]

There is some evidence that mindfulness-based interventions could be especially effective for low SES smokers. A key reason proposed for the socioeconomic inequity in smoking rates is the chronicity of stressors (including financial strain) and the associated anxiety which disproportionately affects disadvantaged communities. [18, 33–35] Higher trait mindfulness (mindfulness as a stable long-term life approach) has been linked indirectly with a lower risk of smoking relapse through decreased stress levels, indicating that the enhanced emotional regulation afforded by mindfulness might be especially beneficial for low SES smokers trying to quit. [36] Practising mindfulness, as a coping strategy, is also important for low SES smokers because they typically have a higher nicotine dependence. [7, 8] Specifically, mindfulness could decrease perceived withdrawal severity by reducing the agitation and negative affect which accompany nicotine withdrawal and promote resilient responses to cravings. [37, 38] Research also indicates that mindfulness-based addiction therapy might help smokers “bounce back” from lapses and regain abstinence at a higher rate compared to CBT and usual care [39].

Research suggests that peer support programs show promising efficacy for promoting smoking cessation in socioeconomically disadvantaged groups. In their systematic review, Ford et al. [40] argue that this is due to the lower baseline levels of social support often available to disadvantaged groups. Furthermore, a barrier to cessation for disadvantaged groups is that they are sceptical of traditional counselling services (e.g., Quitline), anticipating an impersonal and unsupportive experience. [41] Peer mentors can be perceived as more credible than healthcare professionals because they provide experiential knowledge. [42] By sharing their experiences of quitting and speaking as a peer rather than a professional, peer mentors can be positive role models who might be capable of overcoming perceived impediments to services.

The research described above suggests that that an effective, low-cost approach is necessary to support low SES individuals in quitting smoking and reduce the associated health and economic burdens that affect these communities. Setting realistic goals (SRG) and mindfulness training (MT) are both feasible and potentially effective interventions requiring thorough examination for use with low SES smokers. The present study examines the efficacy of these together with mindfulness-integrated CBT (MiCBT) because MiCBT acknowledges the importance of both as well as CBT.

## Methods

The following protocol (version 5, September 9th 2022) follows SPIRIT guidelines for reporting protocols (see Additional file 1). In this four-arm parallel-group RCT of SRG, MT and MiCBT versus an active control (equal allocation ratio), we will deliver the interventions to small groups of smokers to maximise the potential cost-effectiveness. 6-months of these interventions will be followed by 6-months of online peer support and a further 6-month follow-up period. The control group will be directed to optional resources including counselling (Quitline) and information about pharmacological aid. We aim to: (a) test the efficacy of the three interventions (SRG, MT and MiCBT) for smoking cessation and (b) levels of resilience in low SES groups and how this changes during exposure to the interventions, (c) measure the cost-effectiveness and cost-utility of the interventions in low SES groups, and (d) undertake a process evaluation of the different interventions in low SES groups. We hypothesise the following:H1: The proportion of participants who report 14-day period abstinence from smoking at 6 months will be significantly higher for each intervention group compared to the control group.H2: Amongst participants that report 14-day period abstinence at 6 months, the proportion of participants who report 14-day period abstinence at 12 months will be significantly higher for each intervention group compared to the control group.H3: The proportion of participants who report 14-day period prevalence abstinence from smoking at 6 months post-trial (18 months from baseline) will be significantly higher for each intervention group compared to the control group.H4: Levels of resilience measured by the Connor-Davidson CD-25 [43] and ENRICHD Social Support Inventory [44] will be significantly higher for each intervention group compared to the control group at 6, 12 and 18 months post randomisation.H5: The interventions will improve smoking cessation and QALYs at a reasonable and acceptable incremental cost.

In addition, we pose the following research questions for the qualitative component of the study (that pertains to the process evaluation):RQ1: Have the different interventions been implemented and received as intended?RQ2: What are the barriers and facilitators associated with the first research question?RQ3: For whom, and in what circumstance were the interventions effective (and cost-effective) or not, and why?

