### Sample size and power analysis

For the primary outcome of smoking cessation, 182 participants per group is powered to detect an 11.6% difference [47] in the smoking abstinence rates between groups (with 80% power, alpha = 0.05 (two-tailed test) We will account for a 10% drop-out rate, and thus aim to recruit 203 per group (N = 812). Contextually, the smoking cessation rates we used for the sample size calculation (MT = 25.2%, usual care = 13.6%) represent a meaningful population health treatment effect doubling of the rate of successful quit attempts for the lowest SES group (11.4%; [9]).

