### Measures

#### Primary outcome—smoking

The primary outcome is smoking cessation at the 6-month (or 26 week) timepoint. Smoking cessation is defined as 14 days of not smoking cigarettes, determined by two consecutive 7-day periods of self-reported smoking abstinence (“In the last seven days, have you smoked a cigarette, even a puff?”). Participants who meet this criterion at the time of the 6-month mark will be asked to self-administer a saliva test to detect the presence of cotinine (< 30 ng/mL), accurately reflecting abstinence for the preceding 3–4 days. Participants will be instructed to photograph the results and send them to the research team via SMS or email. The purpose of this one-time measurement is to biochemically verify the self-reported smoking cessation outcomes within the study. [48]

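### H2 compares 12-month abstinence only among 6-month quitters, a subset the interventions are expected to change, so it is not a randomised comparison and has only about 25 expected controls

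*Protocol article*

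**What the plan says.** The hypotheses are listed in the opening of Methods. H1 concerns abstinence at 6 months and H3 abstinence at 18 months; neither restricts who is counted. H2 does: "Amongst participants that report 14-day period abstinence at 6 months, the proportion of participants who report 14-day period abstinence at 12 months" is predicted to be significantly higher in each intervention arm than in control. H2 is the only listed cessation hypothesis at 12 months.

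The restricting variable is the self-reported part of the primary endpoint: "The primary outcome is smoking cessation at the 6-month (or 26 week) timepoint".

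The section on sample size covers the primary outcome only. It says that "182 participants per group is powered to detect an 11.6% difference", on rates of "MT = 25.2%, usual care = 13.6" per cent.

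Under Statistical analysis, the Timepoints section schedules cessation assessment at 52 and 78 weeks, among others. The Analyses section plans comparisons of the four groups at each time point, sets alpha at 0.0167 for testing across 6, 12 and 18 months, leaves open a further adjustment for the three comparisons with control, and counts missing smoking data as smoking. It mentions neither the H2 subset nor a method for selection after randomisation.

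**The concern.** Randomisation makes whole arms comparable. It does not make those who have quit by 6 months comparable across arms if treatment affects who quits. H1 predicts that it does. On the planning rates, 11.6 of the 25.2 percentage points of intervention quitters are in excess of control. Those extra quitters may relapse more readily than people who would have quit anyway, or less readily. Either way, the conditional 12-month proportions can differ even if nothing after month 6 had any effect.

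Two things are at stake. An arm that leaves more people abstinent at 12 months could fail H2 or look worse on it, and the reverse error is equally possible. The restriction also shrinks the sample to the quitters, so H2 would detect only very large differences.

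**Working it through.** **1. The plan's own figure.** Inputs from the sample-size section: 13.6% and 25.2%, "with 80% power, alpha = 0.05 (two-tailed test"). With pooled variance under the null and mean rate (0.136 + 0.252)/2 = 0.194:

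n = [1.96 × √(2 × 0.194 × 0.806) + 0.8416 × √(0.136 × 0.864 + 0.252 × 0.748)]² / 0.116² = (1.096 + 0.466)² / 0.01346 = 181.2, so 182 per group (power 80.2%).

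182/0.90 = 202.2, so 203 per group and 4 × 203 = 812. The stated figures reproduce.

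**2. Expected H2 denominators.**

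| Basis | Control | Each intervention arm |
|---|---|---|
| 182 per arm | 182 × 0.136 = 24.8 | 182 × 0.252 = 45.9 |
| 203 per arm | 203 × 0.136 = 27.6 | 203 × 0.252 = 51.2 |

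The second row applies if non-responders stay in the denominator of the 6-month rate as smokers. These are expected counts; a per-protocol set could be smaller.

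**3. What H2 can detect.** The article gives no maintenance rate, so I assume 40% to 70% in control. For control maintenance p₁, intervention maintenance p₂ and subset sizes n₁ and n₂,

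power = Φ[(p₂ − p₁ − z × SE₀)/SE₁],

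where SE₀ uses the pooled proportion, SE₁ the separate ones, and z is 1.96 at alpha 0.05. With 24.8 and 45.9 quitters, p₁ = 0.60 and p₂ = 0.891: SE₀ = 0.1018, SE₁ = 0.1087, and (0.291 − 0.1995)/0.1087 = 0.84, which gives 80% power.

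| Assumed control maintenance | Difference for 80% power, alpha 0.05 | Same, alpha 0.0167 | Power for +20 points, 0.05 | Same, 0.0167 |
|---|---|---|---|---|
| 40% | 33.7 points | 38.3 points | 36% | 21% |
| 50% | 32.0 | 36.0 | 38% | 23% |
| 60% | 29.1 | 32.4 | 44% | 29% |
| 70% | 25.1 | 27.5 | 56% | 41% |

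On the 203 basis, the detectable difference at alpha 0.05 is 32.1 points at 40% maintenance and 24.1 at 70%.

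**4. Selection can push either way.** Assumptions: the 13.6% who would quit under control would also quit under intervention; 60% of them maintain in either arm; a further 11.6% quit only with the intervention and maintain at rate m. Conditional maintenance in the intervention arm is (0.136 × 0.60 + 0.116 × m)/0.252.

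| m | Maintenance among quitters, intervention v control | Abstinent at both 6 and 12 months, all participants, intervention v control |
|---|---|---|
| 40% | 0.1280/0.252 = 50.8% v 60.0% | 12.8% v 8.2% |
| 60% | 0.1512/0.252 = 60.0% v 60.0% | 15.1% v 8.2% |
| 70% | 0.1628/0.252 = 64.6% v 60.0% | 16.3% v 8.2% |

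Those who would quit in either arm have identical maintenance throughout. H2 nevertheless points against the intervention, at no difference, or in its favour, depending only on m, which the trial cannot observe directly.

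**The case against.** Four arguments on the other side carry weight.

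- **An unrestricted 12-month comparison is implied.** Cessation is assessed at 52 weeks, the analysis section compares all four groups at each time point, and H3 is unrestricted at 18 months. An arm with more people abstinent at 12 months would therefore show it somewhere. This limits the damage, but it does not repair the hypothesis as stated.
- **Maintenance among quitters is a sensible question for the peer-support phase.** As description, yes. H2 goes further and predicts a significant advantage over control.
- **The replacement does not isolate peer support either.** This stands. Abstinence among all participants at 12 months carries forward whatever was achieved by month 6.
- **The replacement also has modest power, and low power on a secondary hypothesis is not in itself an error.** This stands too. If 57.3% of intervention quitters maintained against 60% of controls (assumed), joint abstinence would be 0.252 × 0.573 = 14.4% against 0.136 × 0.60 = 8.2%. Power at 182 per arm would be about 47% at alpha 0.05 and 31% at 0.0167. What the replacement gains is validity.

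A reader might infer that H2 is biased against the interventions because the extra quitters must be the more marginal ones. The article gives nothing on their relapse risk, and step 4 shows the direction reversing with that assumption. A reader might also infer that the trial has no valid 12-month cessation comparison. The implied comparison of all groups at 52 weeks speaks against that.

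**Conclusion.** The concern holds as a defect in one secondary hypothesis. H2 makes an efficacy claim in a subset defined by an outcome that treatment is expected to change, and the article offers no method for the selection. Bias may run in either direction, and its size cannot be known from the documents.

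The expected denominators of about 25 and 46 (28 and 51 on the 203 basis) rest only on the planning rates; actual counts will vary. The detectable differences of about 34 down to 25 points at alpha 0.05, and 38 down to 27.5 at 0.0167, rest on my assumed control maintenance of 40% to 70%. Any further adjustment for three comparisons with control would raise them. The primary comparison at 6 months is unaffected by this point.

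**What to change.** Restate H2 on all randomised participants: the proportion in each intervention arm abstinent at 12 months, or at both 6 and 12 months, compared with control. Choose one of the two definitions in advance. Count missing smoking status as smoking, as the analysis section already does. Report maintenance among 6-month quitters by arm as a descriptive figure, with a note that the groups are selected after randomisation.

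No new data are needed. The cost is a documented amendment to one secondary hypothesis of a registered trial that is already recruiting. The question also changes: the restated H2 measures the overall effect at 12 months, including the effect already present at 6 months, so a positive result should not be attributed to peer support. Its modest power should be acknowledged.

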### Participants

We aim to recruit 812 low SES smokers Australia-wide using web-based advertisments. Inclusion/exclusion criteria for this study will require that participants will be aged 18 years or older and have smoked regularly for at least the previous two years, as assessed by the question: “are you a regular smoker (i.e., you have usually smoked at least one cigarette per day for at least the last two years)?” We will only include smokers who are planning to quit, i.e., they answer yes to the question, “are you currently planning to quit smoking cigarettes?” This indicates that the participant is in the preparation stage of the Transtheoretical Model and getting ready to progress to action. [45] Participants must also have a smartphone, have regular internet access, and be willing to spend approximately 14–20 h online to complete the study over an 18-month period.

We define low SES using household income and access to Australian welfare benefits. Smokers will be included if either (a) their weekly household income is below $457 per adult before tax (the Australian poverty line; [46]) or (b) they receive social security benefits, e.g., aged or low-income pension, parenting payments, or disability support payments. Participants will be recruited from all Australian states and territories using online advertisements on social media and news stories on local radio and television. Recruitment will also be promoted via the networks of Project Reference Group members and other stakeholders providing services to low SES populations. Recruitment began on the 3rd of May 2021, and we aim to continue recruitment until the target sample size is reached.

